## Abstract

**Background:**

For prostate cancer treatment, treatment options with minimal side effects are desired. External beam radiation therapy (EBRT) is non-invasive, standard of care and delivered in either conventional fractionation over 8 weeks or with moderate hypo-fractionation over about 5 weeks. Recent advances in radiotherapy technology have made extreme hypo-fractionated stereotactic body radiation therapy (SBRT) of prostate cancer feasible, which has not yet been introduced as a standard treatment method in Germany. Initial results from other countries are promising, but long-term results are not yet available. The aim of this study is to investigate feasibility and effectiveness of SBRT for prostate cancer in Germany.

**Methods/design:**

This German bi-center single group trial (HYPOSTAT) is designed to evaluate feasibility and effectiveness, as measured by toxicity and PSA-response, respectively, of an extreme hypo-fractionated SBRT regimen with five fractions of 7 Gy in treatment of localized low and intermediate risk prostate cancer. The target volume includes the prostate with or without the base of seminal vesicles depending on risk stratification and uncertainty margins that are kept at 3–5 mm. SBRT treatment is delivered with the robotic CyberKnife system, which was recently introduced in Germany. Acute and late toxicity after one year will be evaluated according to Common Terminology Criteria for Adverse Events (CTCAE v. 4.0), Radiation Therapy Oncology Group (RTOG) and International Prostate Symptom Score (IPSS) Scores. The quality of life will be assessed before and after treatment with the EORTC QLQ C30 questionnaire. Hypothesizing that the proportion of patients with grade 2 side effects or higher is less or equal than 2.8%, thus markedly lower than the standard EBRT percentage (17.5%), the recruitment target is 85 patients.

**Discussion:**

The HYPOSTAT trial aims at demonstrating short term feasibility of extreme hypo-fractioned SBRT for the treatment of prostate cancer and might be used as the pilot study for a multi-center multi-platform or for randomized-controlled trials comparing conventional radiotherapy with SBRT for localized prostate cancer in the future. The study concept of patient enrollment, follow up and evaluation by multiple public university clinics and actual patient treatment in dedicated private radiosurgery practices with high-tech radiation equipment is unique for clinical trials.

**Study status:**

The study is ongoing and currently recruiting patients.

**Trial registration:**

Registration number: NCT02635256 (clinicaltrials.gov). Registered 8 December 2015.

## Background

### General treatment strategy for localized prostate cancer

Prostate cancer is the most frequently diagnosed malignant tumor and the third most frequent reason for men’s death in Europe [1]. Current therapy procedures for localized prostate cancer include active surveillance, prostatectomy and radiation therapy, but the optimal therapy regime remains unclear.

Compared to other cancers, prostate cancer is characterized by three specific features: the progression rate is slow, the patient population is old with a median age at diagnosis of approximately 75 years and a specific tumor marker — the prostate specific antigen (PSA) is available to monitor progression even at an early stage [2–5]. Owing to these facts, ‘active surveillance’ is more and more considered as an alternative treatment option for localized low- to intermediate risk prostate cancer [6–8]. During active surveillance, digital rectal exams and annual biopsies are performed and PSA levels are checked regularly and therapeutic intervention is only recommended in case of disease progression (e.g., as measured by increased PSA levels). Some studies have confirmed that early intervention with radical prostatectomy may have no advantage for most patients when compared to active surveillance [9–11].

Local therapies, such as radical prostatectomy or radiation therapy, either in form of external beam radiotherapy (EBRT) or brachytherapy or a combination of both, are indicated if active surveillance is impossible or unwanted or in case of documented disease progression. Radiation therapy is, with respect to tumor control, at least equivalent to radical surgery for all patients with localized disease. The range of side effects is different with the major problems being incontinence after prostatectomy and rectal complications after radiotherapy. However, the overall frequency of side effects seems to be similar [12–18]. The choice of local therapy method, therefore, mainly depends on the patient’s preference and possible contraindications.

Overall, the above mentioned treatment options (active surveillance and local therapy) are compared in several clinical trials: the most recent publication coming from the ProtecT trial [19]. The study group published its 10 year results in 2016 and found that overall survival was not different in the active surveillance and local therapy group; however there seems to be a benefit for local therapy in terms of disease progression and development of metastases [19]. In Germany, a large randomized study (PREFERE) was initiated in 2013 with the objective to compare the different treatment procedures including active surveillance, prostatectomy, brachy-therapy and EBRT for low risk prostate cancer. PREFERE was the largest oncological clinical trial in Germany and financially supported by the German Cancer Aid and includes patients younger than 75 years at diagnosis with a PSA value ≤ 10 ng/ml and a Gleason score ≤ 7a (3 + 4). Approximately 7300 patients were planned to be treated, but the study was recently closed.

### External beam radiotherapy

EBRT for low/intermediate risk prostate cancer is generally carried out with conformal- (3D-CRT) or intensity- and volumetric-modulated radiotherapy (IMRT and VMAT) techniques delivered in conventional fractionation [20–23]. The target organ (prostate, possibly also the seminal vesicles or a part of them) is irradiated with single doses of 1.8–2.0 Gy daily for 5 days a week up to a total dose of 72–78 Gy [20–23]. There is a clear dose-response relationship between tumor control rates and total irradiation doses [24, 25]. However, better local control has not resulted in increased survival. Moreover, almost all studies have also shown an increase of late toxicity at higher doses [24, 25]. For example, a large randomized-controlled trial found that 39% of all patients developed genitourinary (GU) toxicity, and 32% had grade 2 gastrointestinal (GI) toxicities after 4.2 years of follow up [24]. After 1 year, approximately 17.5% of patients had grade 2 late complications in the GU system and 10% developed toxicity in the GI system.

### Rationale for treating localized prostate cancer using hypo-fractionation

In general, conventional fractionation for EBRT with daily doses of 1.8–2.0 Gy is based on the assumption that the cells of the surrounding healthy organs have a lower proliferation rate than the tumor cells and are therefore less reactive to small radiation doses. The cell survival of an organ or tumor after irradiation is generally described by the α/β-value [26] — high proliferating organs or tumors have α/β-values in the order of 10 Gy and very slow proliferating organs or tumors have α/β-values in the order of 2 Gy.

Recent data from various prospective studies suggest a low fractionation sensitivity of prostate cancer [26, 27]. Currently, the α/β-value of prostate cancer is estimated to be approximately 1.5 Gy; thus, lower than the currently estimated α/β-value for late rectal complications, which is approximately 3.0 Gy [28, 29]. This difference in fractionation sensitivity suggests that an advantage might be expected from hypo-fractionated treatment regimens, either with regard to increased local control, reduced late side effects or both. Interestingly, published randomized trials that used moderately hypo-fractionated regimens (e.g., 22 vs. 40 fractions) showed only similar results with regard to biochemical control and even slightly worse side effects compared to standard fractionation [30, 31]. A comprehensive review on the topic of moderate hypofraction for prostate radiotherapy was recently published by a German group [32].

### Treatment results with extreme hypo-fractionation

Following the concept of the assumed radiobiology of prostate cancer to the end, several studies in the USA investigated extreme hypo-fractionated regimens, called stereotactic body radiation therapy (SBRT) or sometimes also called radiosurgery. These studies used 5 fractions, and total doses of 35–37 Gy have been reported recently [33–45]. Up to now, more than 1500 patients with 5 years of follow up were treated in 18 different feasibility studies. Most of the studies used robotic SBRT with the CyberKnife system (Accuray Inc., USA) and active fiducial-based tracking because of well-known prostate motion during treatment [46, 47]. Due to relevant prostate movements during treatment, techniques with image-guidance and motion compensation seem mandatory and a widespread use of extreme hypo-fractionation is currently not recommended [48–51].

In brief, these studies showed excellent biochemical control rates after 1–5 years in the range of 93–100% for low and intermediate risk prostate cancers (PSA value < 20 ng/ml and Gleason score ≤ 7). These studies also demonstrated a low frequency of late side effects with a trend towards more severe side effects if a total dose of 35 Gy in 5 fractions were exceeded. Mild side effects (grade 2) with 35 Gy and 36.25 Gy in 5 fractions were 4% and 10% in the GU system, respectively, and 2% and 4% in the GI system, respectively. Serious GU side effects (grade 3) occurred in only 2% of patients treated with 36.25 Gy. These data are in favor of SBRT when compared to the results of standard fractionated EBRT [24, 25, 35, 37]. Recently, the first results of the Scandinavian HYPO-RT-PC trial comparing 42.7 Gy in 7 fractions versus 78 Gy in 39 fractions confirmed this hypothesis [52] and the randomized controlled HEAT (USA) and PACE (UK) trials are actively recruiting patients.

As the treatment of prostate cancer with extreme hypo-fractionated SBRT has not yet been introduced as common practice in Germany and long-term follow-up data are not yet available internationally, the German Society for Radiation Oncology (DEGRO) and the National Radiation Protection Authority (BfS, Bundesamt fuer Strahlenschutz) have issued a strict recommendation to only treat prostate cancer with extreme hypo-fractionation in prospective clinical trials. This body of work represents the first and currently only clinical trial for hypo-fractionated SBRT for localized prostate cancer (HYPOSTAT) in Germany.

## Methods/design

### General study setting

At the time of study protocol initiation of HYPOSTAT in 2012, two main circumstances were found for Germany with respect to prostate cancer treatment: 1) the PREFERE trial was widely supported and conducted by many institutions, and 2) the CyberKnife, from which most prostate treatment data for hypo-fractionated SBRT originated, was only available in a limited number of centers, most being privately owned. It was therefore intended to initiate a clinical trial that included the private CyberKnife centers as well as excluded patients eligible for the PREFERE trial. The current setting in amendment IV from May 2016 of the HYPOSTAT study (protocol number ZKS-121-003) stipulates that patients are enrolled and followed after treatment by public university medical centers and treated by the CyberKnife system in two private practices. At the time being, this is a unique setting in clinical trial design.

### Study design

The HYPOSTAT study is designed as a prospective observational trial. The hypothesis is that image-guided SBRT with 35 Gy in 5 fractions (7 Gy per fraction) is feasible in the treatment of prostate cancer. The primary endpoint is toxicity to the GI and GU system at 1 year after treatment assessed according to the Common Terminology Criteria for Adverse Events (CTCAE v. 4.0) and Radiation Therapy Oncology Group (RTOG) Scores. Secondary endpoints are PSA-failure-free survival, relapse-free survival, urological function assessed by the International Prostate Symptom Score (IPSS), and Quality of life (QoL) assessed before and after treatment with the European Organization for Research and Treatment of Cancer (EORTC) Quality of Life Questionnaire (QLQ) C30 and the Patient Oriented Prostate Cancer Utility Scale (PORPUS) questionnaire.

### Patient inclusion criteria

Histologically confirmed, locally confined prostate cancerCompleted staging according to the National GuidelinesGleason score ≤ 7PSA < 15 ng/mlProstate volume < 80 cm^3^
IPSS-Score ≤ 12Age > 75 years or Age 70–75 years and either PSA > 10 ng/ml and/or Gleason score = 7b and/or Gleason score = 7a with > 33% positive biopsy cores and/or cT > 2a and/or prostate volume > 60 cm^3^
Informed consent

### Patient exclusion criteria

Treatment in the PREFERE trial possiblePrevious pelvic radiotherapyContraindication against the implantation of fiducial gold markersImmunosuppressive therapyTreatment relevant co-morbiditiesPatient’s inability to understand or comply with the procedures

### Treatment planning and delivery

Treatment will be carried out with a robotic CyberKnife system (Accuracy Inc., USA) using real-time tracking. Three to four fiducial markers will be necessary to identify the location of the prostate during treatment. The distance between two fiducial markers should be ≥ 2 cm. Implantation of fiducial markers should be completed at least 5 days before treatment-planning computed tomography (CT) to reduce the post-implantation migration of the fiducial marker. During planning CT, and on any treatment day, the use of an enema is advised to reduce the maximum rectal diameter. A bladder catheter is not necessarily needed, but a consistent and constant bladder filling of 20–30 ml during planning CT and treatment is recommended.

Gross tumor volume (GTV) is defined as the prostate on the planning magnetic resonance imaging (MRI) for patients with a low-risk profile and as the prostate with the bases of seminal vesicles (1 cm proximal) for all other patients. The clinical tumor volume (CTV) is defined as GTV plus 1–2 mm for patients with low-risk prostate cancer and plus 2 mm for all other patients. The planning target volume is defined as CTV plus an anisotropic margin of 1 mm posterior into the direction of the rectum and 3 mm in all other directions. Organs at risk (OAR) are rectum, bladder, urethra (if identifiable), neurovascular bundles (if identifiable), penile bulb, small bowel, femoral heads and the skin (5 mm thick). The rectum is defined from the inferior level of the anus to the recto-sigmoid junction to give a length of approximately 12 cm.

All patients will be treated with 35 Gy in 5 fractions (7 Gy per fraction) prescribed to the 80–85% isodose (maximum dose = 100%) covering the PTV to 95% (PTV_35Gy_ ≥ 95%). OAR dose limitations (Table 1) are specified according to published guidelines [33–45, 53–56] and the urethral dose reduction technique will be used to minimize risks of side effects [57]. Patients will be treated every second day with a minimum of 36 h between two fractions. The treatment time shall be 1.5 to 2 weeks.

**Table 1 Tab1:** Dose limits for organs at risk relevant for prostate radiosurgery

Organ at risk	Dose limit
Rectum	D_max_ < 38 Gy V_36Gy_ < 1 cm^3^ & < 5% V_29Gy_ < 15 cm^3^ & < 20% V_18Gy_ < 25 cm^3^ & < 50%
Bladder	D_max_ < 38 Gy V_36Gy_ < 10 cm^3^ & < 10% V_18Gy_ < 40%
Urethra	D_max_ < 44 Gy
Penile Bulb	V_30Gy_ < 3 cm^3^ & < 50%
Femoral Heads	V_30Gy_ < 10 cm^3^ V_14,5Gy_ < 5%
Testicle	To be blocked for passing beams
Small Bowel	V_30Gy_ < 1 cm^3^ V_18Gy_ < 5 cm^3^
Neurovascular Bundle	V_38Gy_ < 50%
Skin (5 mm)	D_max_ < 30 Gy

*D*
_*max*_ *=* Maximum Dose, *V*
_*xGy*_ *=* Volume receiving X Gy or more

### Follow-up assessments

The primary endpoint will be the feasibility of extreme hypo-fractionated SBRT in the treatment of prostate cancer assessed 1 year after treatment, as all of the acute and certain intermediate toxicity will be observed in this period. Follow-up visits will occur at 4–6 weeks, 3 months (± 1 week), 6–9 months and 12–15 months after the last day of irradiation. During follow up, side effects will be documented (if any) and the PSA value (at least twice), IPSS and QoL using the PORPUS questionnaire will be documented. The course of the PSA value will be used to declare biochemical failure according the Phoenix definitions. In case of failure to identify disease progression by assessing the PSA value, progression events are defined as radiologically documented disease progression using Response Evaluation Criteria In Solid Tumors (RECIST) Criteria (Revised Guidelines, Version 1.1, 2009). QoL is assessed using the EORTC QLQ C30 questionnaire at the last follow-up visit.

The reasoning for this short follow-up time was due to the nature of the study design being a feasibility trial with a single technique which would serve as the basis for a subsequent multi-institutional multi-platform trial with long term follow-up. I.e., we did not want to overly delay such long term multi-institutional multi-platform study and decided to finish the initial feasibility trial as soon as possible. For long-term evaluation, patients will of course be followed for at least 5 years according to the standard practice for radiotherapy in Germany which additionally will include treatment relevant efficacy, side effects, IPSS and QoL assessments; however, this will not be part of the study protocol.

### Sample size calculation

Based on available data and radiobiological calculations, the frequency of severe toxicity (grade 2 or higher) is expected to be approximately 2.8% for GU and 1.1% for GI toxicity. Eighty-five and fifty-four patients are required to reject proportions of 17.5% and 10% with 78% and 88% power at two-sided significance levels < 5% with the exact binomial test using a Bonferroni-Holm procedure. The aim is therefore to recruit 85 patients in this trail.

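### The printed 78% power does not follow from 85 patients and a GU rate of 17.5% against 2.8%: the exact binomial test gives 99.7%, so the justification for 85 is wrong as written

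*Protocol article*

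**What the plan says.** The section "Sample size calculation" of the protocol article gives the whole calculation in a few lines. The frequency of grade 2 or higher toxicity "is expected to be approximately 2.8% for GU and 1.1% for GI toxicity". It then states that "Eighty-five and fifty-four patients are required to reject proportions of 17.5% and 10% with 78% and 88% power", using an exact binomial test at two-sided levels below 5% with a Bonferroni-Holm procedure, and sets recruitment at 85.

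The order of the figures pairs 17.5% with GU and 10% with GI. Two other places confirm this:

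- Background, External beam radiotherapy: "After 1 year, approximately 17.5% of patients had grade 2 late complications in the GU system and 10% developed toxicity in the GI system".
- Abstract, Methods/design, after naming 2.8% as the hypothesised rate: "thus markedly lower than the standard EBRT percentage (17.5%), the recruitment target is 85 patients".

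The GU null is thus printed consistently as 17.5%. The article prints no rejection count for either endpoint.

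**The concern.** The gap between 2.8% and 17.5% is very wide for a single-proportion test with 85 patients, and power of only 78% is implausible on sight. The narrower GI comparison (1.1% against 10%) is credited with 88% power from only 54 patients, which adds to the doubt.

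Two things are at stake. First, the power and the claim that 85 patients are required form the trial's sample size justification; if they do not follow from the stated inputs, that justification fails. Second, in a single-arm trial the null rate fixes how many events still count as success. If the power figure came from a different null than the one printed, it is unclear whether the printed null is the one the sponsor planned with.

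**Working it through.** **Inputs.** From the sample size section: true rates p1 = 2.8% (GU) and 1.1% (GI); nulls p0 = 17.5% (GU) and 10% (GI); n = 85 and 54; power 78% and 88%; exact binomial, two-sided below 5%, Bonferroni-Holm over two endpoints.

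**Method.** Take the largest c with P(X ≤ c | n, p0) ≤ a, where a is the lower-tail level. Power is P(X ≤ c | n, p1). Unadjusted two-sided 5% gives a = 0.025; the first Holm step (two-sided 2.5%) gives a = 0.0125.

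**1. GI as printed (n = 54, 10% against 1.1%).** At a = 0.025: P(X ≤ 1 | 10%) = 0.0237 and P(X ≤ 2 | 10%) = 0.0834, so c = 1. Power = P(X ≤ 1 | 1.1%) = 0.881. The printed 88% reproduces, and 54 is the smallest n that reaches it. At a = 0.0125, c = 0 and power is 55.0%, so the printed figure is an unadjusted one.

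**2. GU as printed (n = 85, 17.5% against 2.8%).** P(X ≤ 7 | 17.5%) = 0.0122 and P(X ≤ 8 | 17.5%) = 0.0279, so c = 7 at both a = 0.025 and a = 0.0125. Power = P(X ≤ 7 | 2.8%) = 0.997. The printed 78% does not reproduce. Other versions do not help:

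- lower tail 0.05: 99.9%
- minimum-likelihood two-sided test at 0.0125: 99.0%
- normal and arcsine approximations: 98.4% to 100%
- sample sizes swapped between endpoints: 93.6% for GU with 54, 98.5% for GI with 85

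**3. Smallest n with at least 78% power for 17.5% against 2.8%.**

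| Lower tail | n | Reject at | Power |
|---|---|---|---|
| 0.025 (unadjusted) | 30 | ≤ 1 | 79.5% |
| 0.0125 (first Holm step) | 44 | ≤ 2 | 87.5% |

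**4. Where 78% could come from.** Take n = 85, p1 = 2.8%, p0 = 10%, a = 0.025. P(X ≤ 3 | 10%) = 0.0245 and P(X ≤ 4 | 10%) = 0.0643, so c = 3. Power = P(X ≤ 3 | 2.8%) = 0.785, and 85 is the smallest n reaching 78%. Both printed figures match, at the same unadjusted level that reproduces GI.

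The match is not unique in power. With n = 85 and a = 0.025, any null from about 10.0% to 11.6% gives c = 3 and hence 78.5%. Against 17.5%, 78% would need a true GU rate of about 6.8% (c = 7), which the article does not state.

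**5. Power with Holm and all 85 patients in both tests, GU and GI assumed independent.**

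- GU null 17.5%: c = 7 at either step, so GU power is 99.7%. GI: c = 2 at the first step (0.9323) and c = 3 once GU is rejected (0.9853). Power = 0.9323 + (0.9853 − 0.9323) × 0.9973 = 0.985.
- GU null 10%: c = 2 at the first step (0.5735) and c = 3 once GI is rejected (0.7848). Power = 0.5735 + (0.7848 − 0.5735) × 0.9323 = 0.770.

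**6. One patient fewer, GU null 10%, unadjusted.** With n = 84, P(X ≤ 3 | 10%) = 0.0264 exceeds 0.025, so c drops to 2 and power to 58.1%.

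**The case against.** The strongest reply is that the article states one GU null, 17.5%, in every place, and never tests GU against 10%. On that hypothesis the error is conservative: power is far above the printed value, the size of the test (0.0122) is within its level, and losing some evaluable patients does little harm (at 70 to 84 patients unadjusted power stays at or above 98.6%). This is also a condensed article, and a misprint of either the null or the power is possible. All of this stands. It limits the consequences but does not make the printed power, or the claim that 85 are required, correct.

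A reader might go further and infer that both sizes were computed against 10%, so that the trial has two competing GU success rules: up to 7/85 (8.2%) or up to 3/85 (3.5%), with 4 to 7 events passing one and failing the other. The document does not support that as fact. The 10% null is an inference from a numerical match, a small range of nulls gives the same power, and no event boundary is printed. The disputed zone and the drop to 58% at 84 patients exist only if the inference is right.

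Two further points should not be pressed. Sizing each endpoint separately and recruiting the larger number is ordinary practice, so the 54-patient figure is no error. Leaving Holm out of the power costs little with 85 patients: 78.5% against 77.0% under a 10% GU null, and nothing for GU under 17.5%.

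**Conclusion.** The point holds as an arithmetic error in the stated power and in the sample size justification. For the hypothesis printed in the sample size section and the abstract, GU power with 85 patients is 99.7% rather than 78%, and 30 (unadjusted) or 44 (first Holm step) patients would exceed 78%. This rests only on the article's own rates and its named test. Neither printed power reflects the Holm procedure named in the same sentence.

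That the GU figures came from a 10% null is likely, because power and smallest sample size both match at the level that reproduces GI, but it remains unproven. If 17.5% is meant, the trial is overpowered and only the text is wrong. If 10% was meant, the printed null is wrong and the GU success boundary implied by the text is too lenient. The Holm figures assume that GU and GI events are independent.

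**What to change.** Check the sponsor's original calculation and reconcile the GU null with the power before outcomes are known.

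- **If 17.5% stands, as printed throughout:** keep 85 patients. Restate power as 99.7% for GU (reject at ≤ 7/85) and 98.5% for GI at 85 patients with Holm (≤ 3/85, or ≤ 2/85 at the first Holm step), naming the independence assumption. Drop the claim that 85 are required for 78% power.
- **If the calculation was made against 10%:** correct the GU null in the sample size section and the abstract and give its basis, since the Background reports 17.5% for GU. Print the boundary (≤ 3/85, or ≤ 2/85 at the first Holm step), restate GU power as about 77% with Holm, and note that unadjusted power falls to about 58% at 84 evaluable patients.

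The 54-patient figure can stay if it is labelled as the unadjusted GI requirement. The cost is a recomputation and amended wording, with no extra patients; under the second route the stated GU power becomes slightly less favourable.

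### The 78% power for GU toxicity does not follow from the stated design (the inputs give 99.7%), and no rule links the two Holm-adjusted tests to the single feasibility claim

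*Protocol article*

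**What the plan says.** Protocol article, Study design: there is one hypothesis, "The hypothesis is that image-guided SBRT with 35 Gy in 5 fractions (7 Gy per fraction) is feasible in the treatment of prostate cancer". In the same section, "The primary endpoint is toxicity to the GI and GU system at 1 year after treatment". Follow-up assessments words it differently: "The primary endpoint will be the feasibility of extreme hypo-fractionated SBRT in the treatment of prostate cancer assessed 1 year after treatment".

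Protocol article, Sample size calculation: the frequency of grade 2 or higher toxicity "is expected to be approximately 2.8% for GU and 1.1% for GI toxicity". Then: "Eighty-five and fifty-four patients are required to reject proportions of 17.5% and 10% with 78% and 88% power", at two-sided levels below 5%, "with the exact binomial test using a Bonferroni-Holm procedure". The recruitment target is 85.

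Read in order, that sentence pairs GU with 85 patients, a 17.5% null and 78% power, and GI with 54 patients, a 10% null and 88% power. The background section on external beam radiotherapy supports the pairing of the nulls: after one year, "approximately 17.5% of patients had grade 2 late complications in the GU system and 10% developed toxicity in the GI system". The abstract mentions only the comparison of 2.8% with 17.5%.

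**The concern.** Two things do not fit together.

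First, the printed powers. A fall from 17.5% to 2.8% is a large effect for a one-sample test in 85 patients, and 78% looks far too low for it. If a different null was used, either the printed null or the printed power is wrong, and the stated basis for 85 patients is not the real one.

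Second, the link from tests to conclusion. Bonferroni-Holm serves separate claims: either null may be rejected while the other stands. The article has one claim, feasibility, resting on toxicity in both organ systems. If feasibility needs both rejections, each null can be tested at the full level and the adjustment has no purpose. If one is enough, that should be stated. The article says neither, so a significant GI result beside an unimproved GU rate could later be presented as the primary result.

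**Working it through.** **Inputs** (Sample size calculation). GU: null 17.5%, expected 2.8%, n = 85. GI: null 10%, expected 1.1%, n = 54. Exact binomial test, two-sided 5%. Holm over two tests: the smaller p-value is tested at 2.5% and, if it is rejected, the other at 5%.

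**Method.** The critical value c is the largest count with P(X ≤ c | null) ≤ α/2. Power is P(X ≤ c | expected rate).

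**Single-test results**

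| Test | n | Two-sided α | c | Lower tail under null | Power |
|---|---|---|---|---|---|
| GI, 1.1% vs 10% | 54 | 5% | 1 | 0.0237 | 88.1% |
| GI, 1.1% vs 10% | 54 | 2.5% | 0 | 0.0034 | 55.0% |
| GU, 2.8% vs 17.5% | 85 | 5% | 7 | 0.0122 | 99.7% |
| GU, 2.8% vs 17.5% | 85 | 2.5% | 7 | 0.0122 | 99.7% |
| 2.8% vs 10% | 85 | 5% | 3 | 0.0245 | 78.5% |
| 2.8% vs 10% | 85 | 2.5% | 2 | 0.0070 | 57.4% |
| GI, 1.1% vs 10% | 85 | 5% | 3 | 0.0245 | 98.5% |
| GI, 1.1% vs 10% | 85 | 2.5% | 2 | 0.0070 | 93.2% |

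The 88% reproduces. The 78% does not reproduce from its stated inputs at either level. It matches the GU expected rate set against the GI null, unadjusted. Against 17.5%, 78% power at two-sided 5% is first reached with 30 patients and holds from 39 onwards; at 2.5% it takes 44.

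**Full Holm power.** For tests A and B, assuming independence: P(reject A) = P(A at 2.5%) + [P(A at 5%) − P(A at 2.5%)] × P(B at 2.5%).

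- Stated nulls, n = 85 (GU) and 54 (GI). GI: 0.5503 + (0.8808 − 0.5503) × 0.9973 = 0.880. GU: 0.997.
- GU null 10%, n = 85 and 54. GU: 0.5735 + (0.7848 − 0.5735) × 0.5503 = 0.690. GI: 0.5503 + (0.8808 − 0.5503) × 0.5735 = 0.740.
- GU null 10%, n = 85 for both. GU: 0.5735 + (0.7848 − 0.5735) × 0.9323 = 0.770. GI: 0.9323 + (0.9853 − 0.9323) × 0.5735 = 0.963.

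None of these readings makes 78% and 88% Holm powers together. The 88% is a Holm power only where GU is tested against 17.5%, and there GU has 99.7%.

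**Requiring both rejections, n = 85, stated nulls, each at two-sided 5%.** Joint power = 0.9973 × 0.9853 = 0.983 under independence. Whatever the dependence, it lies between 0.9973 + 0.9853 − 1 = 0.983 and 0.985. The probability of rejecting both under Holm is the same 98.3%, because the GU critical value is 7 at both levels.

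**What a one-rejection rule would do.** Take true GU toxicity of 17.5% (no benefit) and GI of 1.1%, with n = 85. P(at least one Holm rejection) = 1 − (1 − 0.0122)(1 − 0.9323) = 0.933. P(both rejected at 5%) = 0.0122 × 0.9853 = 0.012.

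**The case against.** The strongest defence has four parts.

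- **Holm does not define trial success.** A reader might infer that the plan lets GI or GU alone establish feasibility. No section says so; Holm only decides which nulls may be rejected. A condensed article may also leave the mapping to the full protocol. This stands against the stronger reading. What remains is that the article itself fixes a multiplicity procedure beside a single hypothesis that it does not obviously serve.
- **The 93% is not an error rate.** In that scenario the GI null is false, and almost all of the 93% is its correct rejection. The chance of a false GU claim is 1.2% under Holm and under the unadjusted test alike. This stands; the figure shows only what would follow if one rejection were read as feasibility.
- **A reader might infer that both powers were computed ignoring Holm, and that Holm cuts them to 55% and 57%.** Those are first-step figures only. With the stated nulls, the full Holm power for GI at n = 54 is 88.0%, so the printed 88% fits. For GU, the adjustment costs nothing against 17.5%; the discrepancy comes mainly from the null rate. This stands.
- **Requiring both rejections changes nothing numerically at n = 85.** True: 98.3% with or without Holm. The gain is in stating the rule.

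None of this rescues the 78%, which is wrong against its own stated null.

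**Conclusion.** The point holds in a limited form. The printed GU power of 78% is inconsistent with 85 patients and 2.8% against 17.5%, which give 99.7% with or without the first Holm step. A 10% null in place of 17.5% is the only pairing tried that yields it. That substitution is an inference from the arithmetic, not something the article states. The GI power of 88% is correct as printed.

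The article also leaves open whether feasibility needs one rejection or two, while naming a procedure suited to separate claims.

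Neither defect threatens the trial's size or its error control: at 85 patients and the stated rates, Holm power is 99.7% for GU and 98.5% for GI, both above the printed values, and type I error is controlled. What needs correcting is the stated figures and the decision rule. The results rest on the exact test with α/2 in the lower tail; the joint and Holm powers also assume independence of GU and GI events, which matters little with the stated nulls because GU power is so high.

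**What to change.** In Sample size calculation:

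1. Correct the mismatch between the GU null and its power. If 17.5% is the intended null, as the abstract and background indicate, replace the 78%.
2. State the decision rule: feasibility is concluded only if both the GU null (17.5%) and the GI null (10%) are rejected, each by the exact binomial test at two-sided 5%. Delete the Bonferroni-Holm wording, which this rule makes unnecessary.
3. Restate power for 85 patients: 99.7% (GU), 98.5% (GI) and 98.3% (both, assuming independence).

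This takes a few sentences and no extra patients, and should be settled before the outcome data are known. The price is that no confirmatory claim can be made on one organ system alone. If the sponsor wants such claims, Holm can stay, but the text must then say that the two results are separate claims and how they bear on feasibility.
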